### Data analysis plan

The primary outcome parameter will be based on patients who transition to Phase II of the study. The ASD prevalence estimate will be calculated based on the proportion of Phase II participants who meet the ICD-10-DCR and DSM-5 diagnostic criteria for ASD on clinical assessment, with adjustment for selection and non-response, as well as the different study designs for the ID and non-ID patient subgroups.

For the feasibility study, the analyses will be descriptive. For continuous variables, values and SD will be reported; for categorical variables, percentages and SD will be reported. We will use multiple imputation to account for any missing data. For the full-powered study, the generalised linear model will be used to estimate the difference between groups, as well as corresponding OR, 95% CI and p values.

The analyses will be primarily conducted in SPSS (version 26), but for more advanced statistical analyses (such as use of the generalised linear model) and graphical representation, we will use R.

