## Abstract

**Introduction:**

Autism spectrum disorders (ASDs) are associated with difficulties in social interaction, communication and restricted, repetitive behaviours. Much is known about their community prevalence among adults, data on adult inpatients within an acute mental health setting is lacking.

This pilot study aimed to estimate the prevalence of ASDs among adults admitted to acute mental health wards and to examine the association between ASDs and psychiatric and physical comorbidities within this group.

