25 found that children with ASDs experienced significantly higher levels of psychopathology compared with those with ID, a group which in itself is associated with an elevated risk of psychiatric disorder.^26^

However, it is unclear how the burden of psychiatric comorbidity seen in children with ASDs transitions into adult life.^27^ It is essential to understand this natural course of ASDs and its comorbidities in order to develop appropriate services to meet the needs of this patient group.^28^ Additionally, some psychiatric disorders, such as schizophrenia, do not typically manifest until late adolescence onwards,^29^ so child comorbidity studies into such disorders would be of limited value.

A scoping review by Cashin *et al*
30 found a lack of research pertaining to the physical health of individuals with diagnosed ASDs, and that most studies were limited to retrospective analysis of healthcare records rather than involving any form of direct health assessment. Additionally, these studies were focused on individuals with previously recognised ASD diagnosed through routine clinical assessment, rather than having been identified through population-based epidemiological studies. Current evidence suggests that children with ASDs are at greater risk of a range of comorbid physical illness compared with their non-ASD peers, including obesity,^31–33^ epilepsy,^34 35^ asthma,^35^ sleep disorders^36^ and gastrointestinal disorders.^36^ This assertion is further supported in a recent systematic review by Muskens *et al*,^37^ who described medical disorders across a range of medical areas (including immunology, neurology and gastroenterology) as being widespread among children with ASD. However, despite the relative paucity of research in child populations, even less is known about the burden of physical comorbidity among adults with ASDs.^38^

The aims of this prospective pilot study are to estimate the prevalence of ASDs among adults based on acute mental health inpatient units, as well as to examine the association between ASDs and other psychiatric and physical comorbidities within this group.

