### Outcome parameters

The primary outcome parameter for this pilot study is the presence or absence of meeting ICD-10-DCR and DSM-5 diagnostic criteria for ASDs, respectively. Secondary outcome parameters, including the study phase in which the corresponding parameters are collected, are summarised in table 4.

**Table 4 T4:** Summary of secondary outcome parameters

Outcome category	Corresponding parameters	Study phase in which data is collected
Autism questionnaire data	Autism Quotient, AQ^41^ Informant version of the Social Responsiveness Scale, second edition, SRS-A^45^ Self-report and Informant versions of the Adult Social Behaviour Questionnaire, ASBQ^46^	Phase I
Basic demographic information	Date of birth Sex Postcode Ethnic group Employment status Relationship status	Phase I (non-ID participants) Phase II (ID participants)
Mental health history	Date of most recent psychiatric hospital admission Discharge date of most recent psychiatric hospital admission (where applicable) Total number of inpatient psychiatric admissions 2014 Adult Psychiatric Morbidity Survey (APMS) mental illness checklist^13^	Phase I (non-ID participants) Phase II (ID participants)
	The Mental Illness Diagnoses and Treatment section of the 2014 APMS^13^	Phase II
Physical health history	2014 APMS physical health conditions checklist^13^	Phase I (non-ID participants) Phase 2 (ID participants)
	The Physical Health Conditions section of the 2014 APMS^13^	Phase II
General health	EuroQol-5D-5L^47^ data for participants and informants	Phase I
Stigma experience (ID participants only)	Stigma Questionnaire for people with Intellectual Disability, SQID^50^	Phase II (ID participants)

ID, intellectual disability.

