### Sample size justification

The sample size was calculated with direct statistician support, as well as the use of a statistical textbook and related software.^51^ For a significance level of 0.05 and power of 85%, assuming estimates of 1% community ASD prevalence and 5% inpatient ASD prevalence,^15^ a sample size of 374 patients is required. Ideally, we would be subjecting a minimum of 374 patients to Phase II testing. This is because only participants completing Phase II interview assessments will yield data pertaining to the primary outcome variable (ie, the presence or absence of satisfying diagnostic criteria for ASD).

However, in the first instance, around 40 patients (from the minimum of 200 subjected to Phase I testing) will be selected for Phase II testing (via stratified random sampling for non-ID patients, whereas ID patients will progress automatically to Phase II). The Phase I sample size of 200 patients takes into account the probability sampling method for Phase II selection, in addition to allowing for losses to follow-up for Phase I participants invited for Phase II testing. Our results will assume that the data for these 40 patients are representative of the larger group subjected to Phase I testing. Owing to the sample size, the SPRINT study shou

ld be considered a pilot/feasibility study, the intention of which being to establish and further refine the technical, administrative and logistical aspects of the study, with a view towards sample size expansion on its completion. The sample size represents an appropriate sample size for a feasibility study of this type.^52 53^

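### The pilot's only reporting rule for categorical variables is a percentage with an SD, which says nothing about the precision of its binary primary outcome, ASD prevalence

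*Protocol article*

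**What the plan says.** The Introduction states the purpose: "The aims of this prospective pilot study are to estimate the prevalence of ASDs among adults based on acute mental health inpatient units". Under Outcome parameters the endpoint is binary: "The primary outcome parameter for this pilot study is the presence or absence of meeting ICD-10-DCR and DSM-5 diagnostic criteria for ASDs, respectively".

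The Data analysis plan then treats two matters in turn.

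- **Prevalence.** It is the proportion of Phase II participants who meet criteria, "with adjustment for selection and non-response, as well as the different study designs for the ID and non-ID patient subgroups". No standard error or interval is mentioned.
- **Reporting.** "For the feasibility study, the analyses will be descriptive", and "for categorical variables, percentages and SD will be reported". The one confidence interval in the plan comes directly after: "For the full-powered study, the generalised linear model will be used to estimate the difference between groups, as well as corresponding OR, 95% CI".

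The Sample size justification says that 374 patients would ideally undergo Phase II and that around 40 will. Study population splits these into 25±5 non-ID and 15±5 ID patients. Table 1 selects non-ID patients with probabilities from 0.1 (AQ 19 or less) to 1.0 (AQ 40 or more).

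**The concern.** A spread measure belongs beside a prevalence estimate only if it tells the reader how far the estimate might be from the truth. The SD of a yes/no variable cannot do that. It is a function of the percentage and adds nothing to it. It does not respond to the number assessed, the unequal selection probabilities or non-response.

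It can also mislead. Printed in brackets after a prevalence, an SD is easily taken for a standard error, and the two differ here by a factor of √40, about 6.3.

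At stake is the usefulness of the pilot's main figure. It will be published, and it is likely to inform the planned expansion. With about 40 assessed patients, unequal weights and a rare condition, a percentage with an SD would hide the fact that the data are compatible with almost any plausible prevalence.

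**Working it through.** **1. The plan's own figure.** The inputs are in the Sample size justification: 1% community and 5% inpatient prevalence, and "For a significance level of 0.05 and power of 85"%. A two-sided comparison of two proportions with pooled variance under the null gives

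n′ = [1.960·√(2·0.03·0.97) + 1.036·√(0.05·0.95 + 0.01·0.99)]² / 0.04² ≈ 325.03, rounded up to 326.

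With the continuity correction, n = (n′/4)·[1 + √(1 + 4/(n′·0.04))]² ≈ 373.4, rounded up to 374 per group. The stated 374 reproduces, so the sample size figure is not at issue.

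**2. What the stated statistic shows.** For a binary variable, SD = √(p(1−p)). Using the 5% assumption and the ends of the earlier inpatient range cited in the Introduction (1.5% to 9.9%):

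| p | SD (any n) | SE at n = 40, unweighted |
|---|---|---|
| 1.5% | 12.2 points | 1.9 points |
| 5% | 21.8 points | 3.4 points |
| 9.9% | 29.9 points | 4.7 points |

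Here SE = √(p(1−p)/n). At p = 5% it falls from 3.4 points at n = 40 to 1.1 points at n = 374. The SD is 21.8 points in both studies.

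**3. What an interval would show, before weighting.** Exact (Clopper-Pearson) 95% limits for illustrative counts:

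| Cases / n | Estimate | 95% interval |
|---|---|---|
| 0/40 | 0% | 0% to 8.8% |
| 2/40 | 5% | 0.6% to 16.9% |
| 4/40 | 10% | 2.8% to 23.7% |
| 0/25 (non-ID) | 0% | 0% to 13.7% |
| 1/25 (non-ID) | 4% | 0.1% to 20.4% |
| 5/15 (ID) | 33% | 11.8% to 61.6% |

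The interval for 2/40 contains both the 1% community rate and the whole earlier inpatient range.

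**4. Effect of the Table 1 weights (non-ID).** Inverse-probability weights run from 10 (1/0.1) down to 1. The article gives no AQ distribution, so one must be assumed. Over four assumed sets of band proportions, the Kish design effect n·Σw²/(Σw)² is about 1.4 to 1.65, so 25 patients carry the information of about 15 to 18 (25/1.65 and 25/1.4).

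A simulation used these assumptions: AQ normal with mean 20 and SD 7; 185 non-ID patients screened (200 less 15); selection by Table 1; random thinning to 25 completers; true prevalence 5%; logistic AQ-risk slopes from 0 to 0.20 per AQ point; and a weighted ratio estimator. Its results were:

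- Standard error about 4 to 5 points, falling as the slope steepens.
- Chance of finding no case about 7% to 28%, also falling as the slope steepens.
- Expected selected before thinning about 38, with a mean weight of about 4.85. The weights of 25 completers then sum to about 25 × 4.85 = 121, so one case with AQ 19 or less moves the estimate by about 10/121, or 8 points.

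Under these assumptions the standard error is of the same order as the 5% being estimated.

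**The case against.** The strongest reply is that the text does not say what a quick reading suggests. The prevalence sentence and the percentage-with-SD sentence are separate. The first is silent on precision, and the second is a general rule for summarising variables. A reader might infer that the plan excludes a valid measure of uncertainty for prevalence. It does not: an interval is left unmentioned, not ruled out. A reader might also infer that confidence intervals are held back for the full study. That is not supported either, because the interval mentioned there belongs to a group difference and odds ratio from a generalised linear model, not to prevalence.

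It is also fair that a journal article may leave the interval method to a fuller document, that SD may be a slip for standard error, and that the article openly calls the study a pilot and reports 40 against 374. Nor does a variable such as sex or ethnic group need a confidence interval.

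All of this limits the claim without removing it. The point does not rest on an omission. The article names a statistic for categorical variables in the pilot, the primary outcome is such a variable, and the statistic is uninformative. If standard error was meant, the sentence still needs correcting. Pilot status makes an interval more useful, and an interval is compatible with a descriptive analysis. A reader could work out a rough unweighted interval from the counts, but not the weighted one.

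**Conclusion.** The point holds as a reporting error of moderate severity. Followed as written, the only rule that the article gives for categorical variables would put an SD of about 21.8 points beside a 5% prevalence, whatever the sample size, while the exact unweighted 95% interval for 2/40 is 0.6% to 16.9%.

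The SD result is algebra and needs no assumption. The intervals depend only on the illustrative counts. The weighted non-ID figures (standard error about 4 to 5 points, 7% to 28% chance of no case, about 8 points for one low-AQ case) depend on the assumed AQ distribution, the AQ-risk slopes, 185 screened and 25 completers. The base of 185 is itself uncertain, because the Abstract has ID patients bypass Phase I and all 200 might be non-ID.

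Recruitment, sampling, data collection and the point estimate are unaffected, so this does not have to be settled before the study can proceed.

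**What to change.** In the Data analysis plan:

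- Delete the SD for categorical variables. Report n and % for descriptive ones such as sex, ethnic group and employment.
- State that ASD prevalence will be reported for non-ID patients, ID patients and overall, each with a 95% confidence interval. The interval should be design-based, use the selection and non-response weights, and include the imputation variance where imputation is used.
- Name a method that remains valid with few or zero cases, such as Wilson or Clopper-Pearson on the effective sample size. Compute it in R, already planned for the more advanced analyses, with survey methods rather than simple case weights.

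The cost is a few sentences and a few lines of code, with no new data. The downside is that the published interval will be wide, which is a fair account of what about 40 assessed patients can show.

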### Sample size justification

The sample size was calculated with direct statistician support, as well as the use of a statistical textbook and related software.^51^ For a significance level of 0.05 and power of 85%, assuming estimates of 1% community ASD prevalence and 5% inpatient ASD prevalence,^15^ a sample size of 374 patients is required. Ideally, we would be subjecting a minimum of 374 patients to Phase II testing. This is because only participants completing Phase II interview assessments will yield data pertaining to the primary outcome variable (ie, the presence or absence of satisfying diagnostic criteria for ASD).

However, in the first instance, around 40 patients (from the minimum of 200 subjected to Phase I testing) will be selected for Phase II testing (via stratified random sampling for non-ID patients, whereas ID patients will progress automatically to Phase II). The Phase I sample size of 200 patients takes into account the probability sampling method for Phase II selection, in addition to allowing for losses to follow-up for Phase I participants invited for Phase II testing. Our results will assume that the data for these 40 patients are representative of the larger group subjected to Phase I testing. Owing to the sample size, the SPRINT study shou

ld be considered a pilot/feasibility study, the intention of which being to establish and further refine the technical, administrative and logistical aspects of the study, with a view towards sample size expansion on its completion. The sample size represents an appropriate sample size for a feasibility study of this type.^52 53^

### Ethics and dissemination

The written approval of the National Health Service Health Research Authority has been obtained, as well as the local ethics committee of the study centre. Written informed consent is and will be obtained from every participant. Significant modifications to the study protocol will be communicated to relevant members of the research team. Any results from this study will be published in peer-reviewed journals and conference proceedings. Additionally, the study’s findings will be disseminated to all participants, including easy-read versions of the findings for those with IDs.
